### Data Management of Embedded Stepped Wedge Cluster Trial

Data sources are shown in Figure 4 and will include the following: (1) Expanded LifeTrac data entry by TCC on all stroke system patients to include prehospital EMSA items (collected in real-time by TCC communicators), abstracted hospital data collected by stroke coordinators including whether an LVO was confirmed, LVO location, and whether the patient received MT and embedded LifeTrac data collection by TCC on patients with EMS-suspected LVO who meet study entry criteria to both guide and document the prehospital triage process in real-time; (2) Study patient ED and hospital data entered by stroke coordinators into an ADPH REDCap database, and (3) System level data captured by ADPH's Recording of Emergency Medical Services Calls and Urgent-care Environment electronic Patient Care Reports to allow determination of the proportion of Alabama MT patients who undergo TCC Coordinated SBST, county and regional EMS response times, proportion of EMS organizations and stroke centers participating, and data on fidelity and maintenance of implementation. REDCap is a secure, HIPAA-compliant, web-based application for supporting data capture for research studies (41). The ADPH REDCap database was developed specifically for this study and will include applicable NINDS Common Data Elements from ED and hospital medical records including the National Institute of Health Stroke Scale (42, 43) and a structured telephone modified Rankin Scale (44, 45) at 3 months post-stroke.

**Figure 4 F4:**
[figure not shown]
Data sources. (1) Expanded LifeTrac data entry on all stroke system patients with embedded LifeTrac data collection by TCC on study patients to both guide and document the prehospital triage process in real-time; (2) Study patient ED and hospital data entered by stroke coordinators into an ADPH REDCap database, and (3) System level data captured by ADPH's Recording of Emergency Medical Services Calls and Urgent-care Environment electronic Patient Care Reports (ADPH RESCUE ePCR).

Patients entered in the stroke system are assigned a unique TCC number that will enable tracking of the patient and linking of data. We plan to pilot data entry and tracking of patients through different phases (prehospital, ED, hospital) and venues (different EDs) of care by TCC and stroke center coordinators in two EMS regions prior to statewide stroke coordinator training. EMS Regional Agencies will play an important role in ensuring complete data capture from stroke centers by following up with stroke center coordinators. Encrypted ADPH data will be transferred to a UAB REDCap database for additional data cleaning, auditing, and analysis by dedicated study personnel including a data manager (MG) and project manager (SK). Data collection forms including validated stroke assessments are available (Supplementary Material 2). Data will be reviewed with the ADPH on a monthly basis. As this is an observational study of a change in health care policy by the ADPH, there is no data monitoring committee. As noted above, the State Medical Director of the OEMS (WC) will provide medical oversite for the OEMS as implementation goes statewide and provide updates to the Statewide Trauma and Health Systems Advisory Council.

### Sample Size Estimates for Stepped Wedge Cluster Trial

Based on 2018 data, the Alabama stroke system volume is about 7,630 over a 1-year period. Based on our pilot data (15), we estimate exclusion of 10% (763 patients) who are unresponsive or poorly responsive, and 5% (382 patients) with time last known well >24 h. We will allow for 10% missing EMSA data (763 patients), leaving 5,722 patients. Pilot data also indicate that over 1 year ~41% of this population (2,346 patients) will have EMSA ≥ 4 and be eligible for enrollment, 18% of enrolled patients (423 patients) will have LVO and be available for analysis of our primary endpoint, and ~50% of the patients with LVO are treated with MT (211 patients). Thus, for our power analyses, we will use 50% as the reference to examine whether implementation of TCC Coordinated SBST will be associated with a significant increase in the proportion of stroke system patients with suspected LVO who are treated with MT. Because of the Before-After nature of the data, a test that accounts for this dependency is necessary. However, even though these are repeated observations the dependency could be rather weak. Many of the same entities (e.g., hospitals, doctors, and paramedics) will be involve both before and after, the patients are very likely to be different; thus, leading to weaker dependency. To account for this possibility, we varied the strength of the dependency (correlation) from *r* = 0 to 0.5. Because the effect of implementing TCC Coordinated SBST is unknown, we varied the effect from small 10% to large 40% improvement. For a weak dependency of (*r* = 0.1), we would need ~350 subjects before and after to detect a moderate 20% improvement with 80% power at a α = 0.05 significance level. This corresponds to an increase of 35 patients treated with MT after TCC Coordinated SBST implementation. A smaller 15% improvement (increase of 26 patients treated with MT) with stronger dependency (*r* = 0.5) would also require ~350 subjects before and after to obtain 80% power at a α = 0.05 significance level. In either case, this data could be collected in ~20 months. Our sample size estimates are based on statewide stroke system entry volume data. Estimates of study eligibility volume and LVO frequency are based on methodology used in our preliminary study. However, to account for the possibility of smaller stroke system volume, smaller effect size, and/or weaker dependency, we plan on 36 months of data collection. For the proposed 36-month data collection timeline, with potentially 1,200–1,300 total observations, we should have more than adequate statistical power to detect a 15% improvement in the primary endpoint even with a weak dependency (*r* = 0.1) among observations.

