### Patient Population—Inclusion and Exclusion Criteria

The study will include patients entered in the Alabama stroke system by EMS with suspected LVO based on an EMSA ≥ 4 with one point scored for each abnormal response on the 6-item scale. The study will exclude patients with stroke onset while hospitalized, a time last known well ≥24 h prior to initial EMS contact, and patients who only respond to pain or who are unresponsive based on the Alert, responds to Voice, responds to Pain and Unresponsive Scale (19). The flow of patients during the study is shown in Figure 3.

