### Primary Outcome

The primary outcome is change in the proportion of prehospital stroke system patients with suspected LVO who are treated with mechanical thrombectomy before and after implementation of TCC Coordinated SBST. We hypothesize that compared to standard triage, TCC Coordinated SBST will be associated with a significant increase in the proportion of patients encountered by EMS with suspected LVO who are treated with MT.

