### Secondary Outcomes

Consistent with the aims of implementation research, in addition to effectiveness, we seek to fully assess change in the broad public health impact before and after implementation of TCC Coordinated SBST using the RE-AIM (Reach, Effectiveness, Adoption, Implementation, and Maintenance) framework (AIM 2) (38, 39). The public health outcomes of TCC Coordinated SBST across RE-AIM dimensions are shown in Table 3. There may be unintended negative consequences to implementation of TCC Coordinated SBST, including delay in access to tPA and longer EMS response times. We address these concerns by explicitly tracking the impact of the intervention on these outcomes (see Table 3). Another concern is overloading MTCs with patients without LVO due to false positive screens and reducing capacity of MTCs to accept transfers of patients for MT. In part, we are hoping to mitigate against this by adding a designation in Alabama for thrombectomy-capable primary stroke centers. We will also track the proportion of LVO patients requiring inter-facility transfer, the timeliness of transfer, and rate of MT among all confirmed LVO strokes for patients entered into the Alabama Stroke System (see Table 3). As part of the stepped wedge trial, we will collect data on the rate of true positive and false positive LVO screens. Because statewide stroke system data collection will include whether an LVO was confirmed, LVO location, and whether the patient received MT, we will be able to determine the rate of true negative and false negative LVO screens, and accordingly, sensitivity and specificity of prehospital LVO screening.

**Table 3 T3:** RE-AIM framework to evaluate the public health impact of TCC Coordinated SBST.

**RE-AIM dimension**	**Outcomes**	**Data source**
**Reach**	• Proportion of Alabama MT patients who undergo TCC Coordinated SBST	• ADPH RESCUE ePCR and LifeTrac database
	• Differential reach by race, ethnicity, sex, and population density	• ADPH RESCUE ePCR and LifeTrac database
**Effectiveness**	• Proportion and timeliness of MT for EMS-suspected LVO	• LifeTrac and ADPH REDCap databases
	• Proportion and timeliness of MT for all confirmed Stroke System LVO	• LifeTrac and ADPH REDCap databases
	• Proportion and timeliness of tPA treatment	• LifeTrac and ADPH REDCap databases
	• Proportion requiring inter-facility transfer and timeliness of transfer	• LifeTrac and ADPH REDCap databases

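### The power calculation uses only patients who turn out to have LVO (50% baseline), but the primary outcome is defined in all EMS-suspected LVO patients (about 9% baseline)

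*Protocol article*

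**What the plan says.** The Primary Outcome section defines the endpoint as "change in the proportion of prehospital stroke system patients with suspected LVO who are treated with mechanical thrombectomy before and after implementation". Its hypothesis uses the same population: an "increase in the proportion of patients encountered by EMS with suspected LVO who are treated with MT". The Abstract agrees.

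Suspected LVO is a prehospital screening result. The inclusion criteria specify "suspected LVO based on an EMSA ≥ 4 with one point scored for each abnormal response" on the six-item scale. Table 3, under Secondary Outcomes, lists "Proportion and timeliness of MT for EMS-suspected LVO" as an effectiveness outcome, and lists MT among all confirmed stroke system LVO on a separate line.

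The sample size section first counts the screened-positive group: "41% of this population (2,346 patients) will have EMSA ≥ 4 and be eligible for enrollment". It then narrows the group: "18% of enrolled patients (423 patients) will have LVO and be available for analysis of our primary endpoint". About half of those (211) are said to receive MT, and 50% becomes the reference rate. The sentence that adopts this reference still describes the quantity tested as the MT proportion among stroke system patients with suspected LVO.

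From that base the article derives about 350 subjects before and 350 after, a collection time of about 20 months, and 1,200–1,300 observations over 36 months. The Abstract and Study Timeline repeat 80% power for a 15% improvement.

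**The concern.** Two denominators are attached to one primary endpoint, and they differ by a factor of more than five (2,346 against 423 a year). They have different baselines, need different sample sizes and answer different questions. A reader of the Abstract would take the 80% power to apply to the stated outcome, and it does not.

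The choice also affects validity. EMSA status is fixed before the triage decision. LVO status is established at hospital, and the intervention changes which hospital that is. The Intervention section says that non-MTCs vary in imaging capability, and Table 2 lists combined CT/CTA among the optional local strategies. If more LVOs are recognised after implementation, an LVO-only denominator moves with the intervention, and the before/after comparison conditions on a post-triage variable.

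**Working it through.** **1. Patient flow (sample size section)**

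- 7,630 − 763 − 382 − 763 = 5,722
- EMSA ≥ 4: 5,722 × 0.41 = 2,346 a year
- With LVO: 2,346 × 0.18 = 422 (stated as 423)
- Treated with MT: 423 × 0.50 = 211

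The flow reproduces.

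**2. The article's sample sizes**

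The improvements are relative: 35 extra MTs per 350 is 50% to 60% (20%), and 26 per 350 is 50% to 57.5% (15%). I used a two-sided paired-proportions (McNemar) calculation with correlation r:

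- p11 = p1·p2 + r·√(p1·q1·p2·q2), with q = 1 − p
- s = p1 + p2 − 2·p11 (sum of discordant probabilities), and d = p2 − p1
- n = [1.96·√s + 0.842·√(s − d²)]² / d²

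| Scenario | s | d | n per period | Article |
|---|---|---|---|---|
| 50% to 60%, r = 0.1 | 0.451 | 0.100 | 352 | about 350 |
| 50% to 57.5%, r = 0.5 | 0.253 | 0.075 | 350 | about 350 |
| 50% to 57.5%, r = 0.1 | 0.451 | 0.075 | 626 (1,252 in total) | 1,200–1,300 |

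The durations match only the LVO subset: 700/423 × 12 = 19.9 months, and 423 × 3 = 1,269 over 36 months. The calculation is internally correct, but it belongs entirely to the LVO-only set.

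**3. Baseline on the defined endpoint**

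211 / 2,346 = 9.0%. The article does not state this figure. It follows from the article's counts if essentially no EMSA-positive patient without LVO receives MT.

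**4. Power on the defined endpoint**

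Patients in 36 months: 2,346 × 3 = 7,038. I assumed an even split, 3,519 per period, and kept the article's relative effects. Power = Φ{[d·√n − 1.96·√s] / √(s − d²)}.

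| | Independent | r = 0.1 | r = 0.5 |
|---|---|---|---|
| n per period for 80% power, 15% relative (9.0% to 10.35%) | 7,526 | 6,778 | 3,774 |
| n per period for 80% power, 20% relative (9.0% to 10.8%) | 4,321 | 3,893 | 2,171 |
| Power at 3,519 per period, 15% relative | 48% | 52% | 77% |
| Power at 3,519 per period, 20% relative | 71% | 76% | 95% |
| Relative improvement detectable with 80% power | about 22% | about 21% | about 15.6% |

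Read literally, the Abstract's claim of 1,200–1,300 observations (600–650 per period) on the suspected-LVO endpoint gives 13–14% power for a 15% improvement at r = 0.1, and 20–21% at r = 0.5.

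**5. If the LVO-only denominator were analysed instead (illustration)**

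Take the 423 as the LVOs confirmed before implementation, 211 of them treated: 211/423 = 49.9%. The confirmation rates below are assumptions, not figures from the article, and MT counts are held fixed.

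- 85% confirmed before, 100% after: denominator 423/0.85 = 498; 211/498 = 42.4%, a relative change of −15%
- 90% confirmed before, 100% after: denominator 423/0.90 = 470; 211/470 = 44.9%, a relative change of −10%
- If the newly confirmed patients received MT at the same rate of about 50%, the shift would be zero

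**The case against.** **The LVO-only set may be the intended endpoint.** The sample size section expressly names the LVO patients as those available for the primary analysis, so the Primary Outcome wording could be the loose part. The eligibility criteria define who enters the study, not necessarily the outcome denominator. Table 3's confirmed-LVO line covers all stroke system LVO, including screen-negative patients, so by itself it does not rule out a primary set of EMSA-positive patients with LVO. This is a fair reading of one section. But no text restricts the primary outcome to patients with LVO, and the sample size section itself applies the 50% to patients with suspected LVO. The contradiction remains on either reading.

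**Independent-sample power is the least favourable case.** This stands in part. At r = 0.5 power rises to 77% for a 15% improvement and exceeds 80% for a 20% improvement. Across the article's range of r, however, 80% for a 15% improvement is never reached. At r = 0.1, where the article claims more than adequate power, it is 52%.

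**The ascertainment bias is speculative.** The confirmation rates are illustrative, CT/CTA is optional in Table 2, and the illustrated shift runs against the hypothesis and vanishes if newly confirmed patients are treated at the same rate. All of this is right. The bias is possible rather than built in, and its size is unknown. It is a reason to prefer a denominator fixed before triage, not an estimate of error.

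**Nothing is miscalculated, and an interim analysis can revisit power.** The arithmetic is indeed sound for the set it uses. The planned interim look can update power, but it cannot settle which patients form the denominator.

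**Conclusion.** The concern holds. The stated power is for MT among patients with LVO at a 50% baseline, while the primary outcome is MT among all EMSA ≥ 4 patients at a baseline of about 9%. On the defined endpoint, 36 months of data give 48% to 77% power for a 15% relative improvement, depending on r, against the 80% claimed.

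These figures assume negligible MT in patients without LVO (any would raise the 9% slightly), an even before/after split with no patients lost to the training periods, and the article's own paired before/after method. They make no allowance for clustering in six regions or for time trends. The mismatch between the sections depends on none of these assumptions. It should be corrected before data accrue; the Study Timeline says enrollment was still pending.

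**What to change.** - **Primary Outcome:** state that the denominator is all eligible EMSA ≥ 4 patients, whatever their final diagnosis. This matches the Abstract, the inclusion criteria and Table 3.
- **Sample size section:** replace the 423 a year available for the primary endpoint with about 2,346 a year (about 7,000 over 36 months), and the 50% reference with about 9%, saying how it is derived.
- **Abstract, sample size section and Study Timeline:** restate power and the detectable effect in percentage points over the planned range of r. For example, on the assumptions above, 80% power corresponds to 9.0% rising to about 11.0% (independent), 10.9% (r = 0.1) or 10.4% (r = 0.5).
- **Secondary outcomes:** keep MT among confirmed LVO as a labelled secondary outcome, noting that its denominator depends on hospital ascertainment.

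The cost is rewording and one re-run power table. No extra patients or data are needed, because LifeTrac is already planned to record MT for all stroke system patients. The stated power becomes less favourable.

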## Abstract

**Background:** Mechanical thrombectomy (MT) can improve the outcomes of patients with large vessel occlusion (LVO), but a minority of patients with LVO are treated and there are disparities in timely access to MT. In part, this is because in most regions, including Alabama, the emergency medical service (EMS) transports all patients with suspected stroke, regardless of severity, to the nearest stroke center. Consequently, patients with LVO may experience delayed arrival at stroke centers with MT capability and worse outcomes. Alabama's trauma communications center (TCC) coordinates EMS transport of trauma patients by trauma severity and regional hospital capability. Our aims are to develop a severity-based stroke triage (SBST) care model based on Alabama's trauma system, compare the effectiveness of this care pathway to current stroke triage in Alabama for improving broad, equitable, and timely access to MT, and explore stakeholder perceptions of the intervention's feasibility, appropriateness, and acceptability.

**Methods:** This is a hybrid type 1 effectiveness-implementation study with a multi-phase mixed methods sequential design and an embedded observational stepped wedge cluster trial. We will extend TCC guided stroke severity assessment to all EMS regions in Alabama; conduct stakeholder interviews and focus groups to aid in development of region and hospital specific prehospital and inter-facility stroke triage plans for patients with suspected LVO; implement a phased rollout of TCC Coordinated SBST across Alabama's six EMS regions; and conduct stakeholder surveys and interviews to assess context-specific perceptions of the intervention. The primary outcome is the change in proportion of prehospital stroke system patients with suspected LVO who are treated with MT before and after implementation of TCC Coordinated SBST. Secondary outcomes include change in broad public health impact before and after implementation and stakeholder perceptions of the intervention's feasibility, appropriateness, and acceptability using a mixed methods approach. With 1200 to 1300 total observations over 36 months, we have 80% power to detect a 15% improvement in the primary endpoint.

**Discussion:** This project, if successful, can demonstrate how the trauma system infrastructure can serve as the basis for a more integrated and effective system of emergency stroke care.

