This project proposes to leverage existing trauma system infrastructure as the basis for a more integrated and effective system of emergency stroke care in Alabama. In our preliminary study, we established the feasibility of improving prehospital LVO recognition by establishing unique real-time TCC directed performance of the Emergency Medical Stroke Assessment (EMSA) in the Birmingham region (15). The intervention was designed to address three barriers to prehospital stroke care, including limited stroke-specific training of EMS, infrequent exposure of individual EMS providers to stroke, and limited feedback on performance (16, 17), by focusing training, experience, and feedback on a small number of Alabama TCC paramedic communicators. The Alabama Department of Public Health (ADPH) has initiated a 5-year statewide quality improvement program of TCC Coordinated SBST which aims to transform the acute stroke care system by coordinating prehospital and inter-facility emergency stroke care. This provides a “natural experiment” allowing assessment of both the public health impact and “how and why” of implementation of an innovative acute stroke care model.

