### Design of the Stepped Wedge Cluster Trial

This is a hybrid type 1 effectiveness-implementation study with a multi-phase mixed methods sequential design and an embedded observational stepped wedge cluster trial. For an overview of how the study elements fit together see the study flowchart (Figure 2). The change in health care policy by the ADPH allows a natural experiment. Given available resources and the complexity of the intervention, the ADPH has planned a phased rollout, lending itself to analysis as a stepped wedge cluster trial with each EMS region serving as a cluster (21, 22). A stepped wedge cluster trial is appropriate given the existing evidence in support of stroke system change, the logistical need for sequential rollout, and the plan for the entire state (i.e., all clusters) to eventually implement the system change. This design will facilitate modeling the impact of time on the effectiveness of TCC Coordinated SBST. This study will broadly and equitably target a population of stroke patients of all ages, sexes, races, and ethnicities. A strength of this study is that at least 50% of subjects will be women and over one-third of the enrolled patients will be African Americans based on census data. As the study involves rural and urban regions and stroke centers of all levels across the State, we will gain information regarding the impact on resources (e.g., EMS response times for non-stroke conditions), benefits, and potential risks (e.g., delay to tPA treatment and other unintended consequences) of implementation across a wide range of service delivery contexts. Finally, because the trial is embedded within expanded LifeTrac data collection on all stroke system patients as well as system level data captured by ADPH, we will be able to evaluate its public health impact.

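### The 80% power claim comes from a paired before/after formula with no region, step or calendar-time term; none of the stepped wedge calculations tried here reaches 80%

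*Protocol article*

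**What the plan says.** The Abstract claims: "With 1200 to 1300 total observations over 36 months, we have 80% power to detect a 15% improvement in the primary endpoint". The section Sample Size Estimates for Stepped Wedge Cluster Trial goes further: "we should have more than adequate statistical power to detect a 15% improvement in the primary endpoint even with a weak dependency" (r = 0.1). Study Timeline relies on the same calculation to justify 36 months of patient data collection.

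The sample size section sets the baseline: "for our power analyses, we will use 50% as the reference". It then gives two worked cases. For r = 0.1, "we would need ~350 subjects before and after to detect a moderate 20% improvement with 80% power at a α = 0.05 significance level", which it equates to 35 more treated patients. The second case is described as "A smaller 15% improvement (increase of 26 patients treated with MT) with stronger dependency" (r = 0.5), again with about 350 per phase. Since 35/350 is 10 points and 26/350 is about 7.5 points, the percentages are relative: 50% to 60%, and 50% to 57.5%.

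On the dependency, the section concedes that "the patients are very likely to be different; thus, leading to weaker dependency".

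The design section describes "analysis as a stepped wedge cluster trial with each EMS region serving as a cluster" and says the design will help to model the impact of time. Randomization states that the health department sets the rollout order. Statistical Analysis of Stepped Wedge Data plans mixed models and generalized estimating equations with a logit link for observations repeated over time.

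**The concern.** The power method and the design do not match. A paired formula lets correlation cancel variance because each unit is seen under both conditions. Here different patients are seen in each phase, so at patient level there is nothing to cancel.

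What the phases do share is region, and the intervention is switched on region by region over calendar time. Because the order is not randomised and every region moves from control to intervention, the treatment effect is confounded with any secular trend in thrombectomy unless time is modelled. Modelling time costs precision, and the calculation allows nothing for it. It also contains no number of clusters, number of steps or ICC.

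At stake is how a non-significant result would be read. A reader who believes the study had 80% power for 7.5 points may take a null result as evidence against an effect of that size. The Interim Analysis section also plans to use primary-endpoint data to guide further power analysis, so the same method could carry forward.

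**Working it through.** **Inputs from the protocol article.** Baseline 50%; target 57.5% (15% relative) or 60% (20% relative); α = 0.05 (two-sided reproduces the stated numbers); power 80%; r = 0.1 or 0.5; 423 analysable patients a year × 3 years = 1,269, within the stated 1,200–1,300, so about 600–650 per phase; six regions as clusters.

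**Inputs assumed here.** ICC 0 to 0.10, step timing, equal region sizes and categorical period effects. The text gives no ICC and no step dates, and Figure 5 is not available.

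**Step 1: reproduce the plan.** The paired-proportions formula is

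n = (1.96 + 0.842)² × [p₁q₁ + p₂q₂ − 2r√(p₁q₁p₂q₂)] / (p₂ − p₁)², with (1.96 + 0.842)² ≈ 7.849 before rounding the quantiles.

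- 50% to 60%, r = 0.1: 7.849 × (0.25 + 0.24 − 0.0490)/0.01 = 346. Stated: about 350.
- 50% to 57.5%, r = 0.5: 7.849 × (0.25 + 0.2444 − 0.2472)/0.005625 = 345. Stated: about 350.
- 50% to 57.5%, r = 0.1: 7.849 × 0.4449/0.005625 = 621 per phase.

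A McNemar version gives 352, 350 and 626. The source of the figures is therefore clear.

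Power for the 36-month claim is Φ(0.075 × √(n/0.4449) − 1.96):
- n = 600: Φ(0.79) = 79%
- n = 650: Φ(0.91) = 82%

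**Step 2: remove the pairing and change nothing else (r = 0).**

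- Required: 7.849 × 0.4944/0.005625 = 690 per phase, or 1,380 in total.
- Power at 600: Φ(0.075 × √(600/0.4944) − 1.96) = Φ(0.65) = 74%.
- Power at 650: Φ(0.76) = 78%.

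This step needs no assumption about ICC or steps.

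**Step 3: stepped wedge calculation.** Cross-sectional Hussey–Hughes model: random region effect, fixed period effects, treatment indicator, total variance p̄(1 − p̄) with p̄ = 0.5375, and generalised least squares for the standard error (SE). Power = Φ(0.075/SE − 1.96). Six equal regions, 1,269 observations.

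| ICC | SE, one region per step (7 periods) | Power | Power, three steps of two regions | Power, two steps of three regions | Power, one region per step, no time term |
|---|---|---|---|---|---|
| 0 | 0.0376 | 51.5% | 43% | 34% | 76% |
| 0.01 | 0.0444 | 39% | 34% | 28% | 69% |
| 0.02 | 0.0460 | 37% | 32% | 27% | 68% |
| 0.05 | 0.0470 | 36% | 32% | 26% | 68% |
| 0.10 | 0.0464 | 36.5% | 32% | 27% | 70% |

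The most favourable schedule tried with time effects (first region at month 3, then one every six months, ICC 0) gives 58%. Excluding one to three training months per region lowers the one-region-per-step figure (36 monthly periods) to 50–45% at ICC 0 and 34–30% at ICC 0.05.

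**Step 4: detectable effect at 80% power.** One region per step, 1,269 observations: about 10.5 points at ICC 0, 12.4 at 0.01 and 13.1 at 0.05, against the claimed 7.5.

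**The case against.** The strongest reply is that the large shortfall is conditional. The step schedule and ICC are assumed, and the analysis section names the model family without fixing its time terms, a detail an article may leave to the analysis plan. This stands. It is why the stepped wedge figures must be given as a range. A reader might infer that the design simply has 35–50% power; the documents do not support stating that as fact, and grouped steps fall below it.

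Second, the pairing error alone is modest. The section varies r, bases its final claim on r = 0.1, and removing the pairing costs only 4–5 points. That also stands, but it is enough to take the claim below 80%.

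Third, r might be meant as correlation through shared hospitals or regions. Over ICC 0–0.10, the six-region model without time terms gives 68–76% at 1,269 observations, no better than independence.

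Fourth, the planned interim analysis could update the power. It may help later, but it does not repair the published figure.

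A reader might also infer that the 50% baseline is too high statewide, because the pilot was in the Birmingham region, and that power is lower still. The documents give no statewide baseline. At an assumed 40% baseline the loss appears only if the effect is held at 15% relative (6 points, 56–59% in a two-sample test). Held at 7.5 points, power is 75–78%. That argument is not part of this point.

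**Conclusion.** The concern holds as a mismatch between power method and design. It is not an arithmetic slip, since the plan's numbers reproduce.

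Two conclusions need no outside assumption. Power is borderline rather than more than adequate on the plan's own formula, and it falls below 80% once the patients are treated as different people.

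The size of the further loss depends on ICC, step timing and time coding. Under the assumptions shown, calendar-period effects bring power to about 51% at ICC 0 and 36–39% at ICC 0.01–0.10 with one region per step, and to about 26–43% with grouped steps. None of the variants with different patients reaches 80%. Because a stated power in the Abstract is unsupported, it should be corrected.

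**What to change.** Replace the paired calculation with a stepped wedge calculation that includes region effects, calendar-period effects, the health department's actual rollout schedule and a stated ICC range. Say how training months are counted.

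In the Abstract, the sample size section and Study Timeline, restate (a) power for a 7.5-point gain and (b) the effect detectable at 80% power in absolute points, each as a range under stated assumptions. For one region per step, (b) is about 10.5 points at ICC 0 to about 13 points at ICC 0.05. Delete the statement that power is more than adequate. Use the same method in any interim power update.

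The cost is a few hours of recalculation and rewording, and a less favourable published power. The fix adds no enrolment.
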